### Operative Assessment

All patients with a single tooth missing in the cleft area will undergo preoperative screening using an orthopantogram (OPG) supplemented with an intraoral periapical radiograph (IOPAR) and bone mapping to determine the need for tertiary grafting. Prior to tertiary grafting, all patients will have the Oral Hygiene Index-Simplified (OHI-S) recorded followed by conduction of oral prophylaxis [11]. Following standard procedure guidelines, bone grafting will be done by a single operator using either an autologous symphyseal bone graft or iliac bone graft, depending on the amount of bone required [12-14]. Before proceeding with implant surgery, the OHI-S will be re-assessed and compared with the previously recorded observations. This will help to determine the patients’ attitudes towards oral health and their motivation towards maintaining oral hygiene. Cone beam computed tomography (CBCT) will be recorded 3-6 months after grafting to evaluate the integration of the grafted bone and plan implant placement. Before proceeding with implant surgery, the OHI-S will be re-assessed and compared with the previously recorded observations. In all patients, titanium dental implants (TitanGrade 4, blasted etched implant surface, Bredent GmbH Co, Senden, Germany) will be placed following a one-stage protocol. Additional bone graft material will be used to ensure complete bony coverage of the dental implant surface, if required. The implants will be placed slightly subcrestally, and the primary implant stability will be clinically evaluated by measuring implant stability quotient (ISQ) values using a Penguin^RFA^ device. The obtained values will be interpreted as follows [15]: ISQ ≥70: high initial stability and suitable for immediate loading; ISQ 55-70: moderate stability; ISQ ≤55: low/questionable stability and not suitable for immediate loading. Following the immediate loading protocol, all implants will be loaded with a provisional prosthesis made of autopolymerizing resin (ie, a provisional prosthesis will be placed within 7 days of dental implant placement) [16]. All patients will be educated about oral hygiene habits to ensure proper care of the placed implant and prosthesis along with use of a 0.12% chlorhexidine rinse for 30 seconds at least twice a day [17].

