### Sample Size Calculation

A recent study showed a success rate of 95% for dental implant–based treatment in cleft patients [10]. With a type I error of 5%, confidence interval of 95%, and 8% margin of error, a sample size of 28 dental implants was obtained. Considering 5% loss to follow-up, an additional 2 dental implants will be placed. Thus, a total sample size of 30 dental implants in sequential patients will be considered for the proposed study.

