### Exclusion Criteria

Patients will be excluded when they are not willing to participate and follow-up for the prescribed study duration, have a syndromic cleft, do not require tertiary bone grafting, are unable to maintain oral hygiene (patients with a lack of manual dexterity or any kind of hand skeletal deformity), and have a history of bruxism and/or smoking.

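### The OHI-S change is read as patient motivation, but a professional cleaning lies between the two scores; the pre-implant score itself is the better hygiene measure

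*Protocol article*

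**What the plan says.** Three statements in the Operative Assessment section of the protocol article bear on this point.

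- **First score, then cleaning:** "Prior to tertiary grafting, all patients will have the Oral Hygiene Index-Simplified (OHI-S) recorded followed by conduction of oral prophylaxis".
- **Second score and its comparator:** "Before proceeding with implant surgery, the OHI-S will be re-assessed and compared with the previously recorded observations". The only earlier OHI-S described is the one taken before the cleaning.
- **Meaning given to the comparison:** it is said to help determine patients' "attitudes towards oral health and their motivation towards maintaining oral hygiene".

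Timing can only be inferred. The planning scan is placed as follows: "Cone beam computed tomography (CBCT) will be recorded 3-6 months after grafting". The sentence on re-scoring appears twice, once before and once after the scan is mentioned, so the exact moment of the second score is not settled. The only hygiene education the section describes comes after the loading step: "All patients will be educated about oral hygiene habits to ensure proper care of the placed implant and prosthesis".

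**The concern.** A before/after difference can be read as patient behaviour only if nothing else that moves the score happens in between. Here a procedure intended to remove deposits is applied to every patient directly after the first score. The OHI-S change is therefore the sum of two parts: what the clinician removed and has not yet re-formed, and any real change in home care. The trial has a single arm, so there is no uncleaned comparison group to separate them.

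Two patients with equally constant habits could show different changes simply because one had more removable deposit at the start. A patient who already cleaned well has little room to improve and could look unmotivated. What is at stake is whether a stated descriptor of the patients means what the protocol says it means.

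**Working it through.** The plan states no figure for the OHI-S, so there is nothing to reproduce. The sample size of 30 implants does not depend on this point. The check has two steps.

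**Step 1. What the difference contains.** Let S1 be the pre-prophylaxis score, D the part of S1 removed by cleaning, f the fraction of D that has re-formed by the second score, and H the reduction due to better home care. Then

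S2 = S1 − D(1 − f) − H, so S1 − S2 = D(1 − f) + H.

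One observed difference cannot yield both D(1 − f) and H. With unchanged habits (H = 0) the apparent relative improvement is D(1 − f)/S1.

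An example with assumed values, none from the protocol: S1 = 2.0 and D = 0.8, habits unchanged.

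| Re-formed fraction f | S2 | Apparent improvement |
|---|---|---|
| 1 (all) | 2.0 − 0.8 × 0 = 2.0 | 0% |
| 0.5 | 2.0 − 0.8 × 0.5 = 1.6 | 0.4/2.0 = 20% |
| 0 (none) | 2.0 − 0.8 × 1 = 1.2 | 0.8/2.0 = 40% |

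The pair 2.0 and 1.2 also fits full re-formation with a real home-care gain of H = 0.8. The data cannot tell the two apart.

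**Step 2. How large the artefact could be over the likely interval.** Assume that cleaning takes the score to 0, habits do not change, and the score returns exponentially to its habitual level with time constant τ. The apparent improvement at time t is then exp(−t/τ). The times of 3 and 6 months come from the scan window after grafting, on the inference that the second score falls near it. Prophylaxis precedes grafting, so the true interval is somewhat longer. The values of τ are assumptions.

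| τ (months) | t = 3 months | t = 6 months |
|---|---|---|
| 0.25 | 0% | 0% |
| 1 | exp(−3) = 5.0% | exp(−6) = 0.2% |
| 3 | exp(−1) = 36.8% | exp(−2) = 13.5% |
| 6 | exp(−0.5) = 60.7% | exp(−1) = 36.8% |

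The artefact ranges from nil to large according to an input that the protocol does not give.

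**The case against.** The strongest reply is that little depends on this comparison. The OHI-S change is absent from the aim and objectives, from the 3- and 9-month parameters under Follow-Up, from the follow-up items of the record sheet (which list gingival and plaque indices), and from the analyses named under Results. No threshold or surgical decision is attached to it. The protocol claims only that the comparison helps to determine attitudes, which is a soft clinical remark. After some months much of the second score may consist of newly formed deposit, and that does reflect home care. All of this stands, and it makes the point minor. It does not rescue the stated reading of the difference.

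A reader might go further in four ways that the protocol does not support.

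- **False assurance about an exclusion criterion.** Patients are excluded who "are unable to maintain oral hygiene", but the same sentence explains this by poor manual dexterity or hand deformity. That is physical inability, not low motivation, and the OHI-S change is not used to judge it.
- **A distorted predictor analysis.** A binary logistic analysis of predictors is planned, but the OHI-S is not named as one of them.
- **A bias that favours the least motivated.** This equates a high first score with low motivation, which is itself an inference from score to attitude. Regression to the mean cannot be sized either: no reliability figure is given and patients are not selected on the OHI-S.
- **A definite artefact of 20–40%.** Those values follow from assumed inputs, and full re-formation gives 0%.

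**Conclusion.** The point holds in a limited form. The sequence of score, cleaning, grafting and second score is explicit, and so is the interpretation placed on the comparison. The difference cannot be attributed to attitude or motivation, because professional cleaning is part of it and the design offers nothing to separate the two. An unchanged patient may show improvement; the protocol does not allow the claim that such a patient will.

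The size is unknown. The 0–61% range at 3 months and 0–37% at 6 months rests entirely on the assumed recovery model, time constants and interval. No estimate of implant success, test, sample size or eligibility decision is affected. This is an inexpensive improvement to an ancillary descriptor, not a threat to the trial's main result.

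**What to change.** In Operative Assessment, change the reading of the two scores.

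1. Use the pre-implant OHI-S value itself as the measure of hygiene maintenance. Because "all patients will have the Oral Hygiene Index-Simplified (OHI-S) recorded followed by conduction of oral prophylaxis", every patient reaches that score after a common professional cleaning.
2. Keep the pre-prophylaxis score as a baseline descriptor, or as a covariate if an adjusted summary of the pre-implant score is wanted.
3. Drop the statement that the comparison shows attitude and motivation. If the raw change is still reported, describe it as the combined effect of prophylaxis and home care.

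The same edit can merge the duplicated re-scoring sentence, so that the text says once when the second score is taken. The cost is wording only, since both scores are already planned. An additional score straight after prophylaxis would add little, because deposits have just been removed at that moment.

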**Objective:**

This protocol is for a single-arm clinical trial aimed at determining the treatment outcome of immediately loaded dental implants in patients with a nonsyndromic orofacial cleft.

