**Results:**

A total of 30 dental implants will be placed in patients with a nonsyndromic orofacial cleft. Obtained results will be statistically analyzed to determine the treatment outcomes and success.

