**Conclusions:**

This study will help determine the feasibility of immediately loaded dental implants in compromised bone sites such as those presented in cleft patients and will help in generating findings that can be used to fill the lacunae currently present in the holistic treatment of cleft patients.

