## Introduction

### Background

Orofacial cleft is the most common congenital anomaly, with an incidence of 1 in 700 to 1 in 1000 live births across different populations [1]. India reports around 28,600 cleft cases every year with a prevalence of 1.09 in 1000 live births [2]. Cleft can be unilateral or bilateral, occurring either alone or a combination of lip and palate, with or without the involvement of the alveolar process. Complete clefting of the lip that involves the full height is often associated with cleft of the alveolus. In addition to compromised aesthetics and disoriented attachment of musculature leading to compromised functionality, these patients also suffer from various dental anomalies [3]. Tooth agenesis affecting the maxillary lateral incisor in the cleft region is the most commonly found anomaly followed by crowding and delayed development [4,5]. All of these defects in cumulation compromise the patient’s quality of life, and each case poses a challenge for the multidisciplinary health care team due to the unique presentation.

Prosthetic rehabilitation plays a triple role of improving aesthetics, phonetics, and functionality of the patient [6]. Use of dental implants has increasingly become popular, as they help in maintaining the bone dimensions in the reconstructed region along with provision of improved aesthetics compared to conventional replacement options. Dental implant can be opted for only when the patient has reached skeletal maturity so as to avoid potential growth hindrance. Postinsertion, an implant requires a healing period of 3-6 months to firmly integrate with the underlying bone, which is then adequately loaded with a prosthesis. Considering the long treatment duration and compromised aesthetics already incurred by the patient, it is necessary to develop protocols that help reduce the rehabilitation time. Immediate implant loading is one such measure wherein acceptable initial implant stability enables implant loading in as little time as 1 week. This would not only decrease time lapse in 2 consecutive rehabilitative procedures but also help improve the patient’s psychological acceptance. Most studies presented have performed implant loading after the universally followed protocol of 6 months [7], while a few studies have also demonstrated loading after 3 months [8]. Only 1 study has been conducted so far that presented the results of immediate or early implant loading, but it was a retrospective analysis [8,9].

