### Follow-Up

All patients will undergo 2 clinical follow ups, 3 months and 9 months after implant placement. At the first follow-up after a period of 3 months following immediate implant loading, the provisional prosthesis will be removed, and clinical and radiological parameters will be measured. Clinical parameters will include probing depth, bleeding on probing, suppuration, pain or tenderness in the implant area, and implant stability using ISQ values. The implant will then be loaded with a definitive prosthesis, and a CBCT will be recorded. A second follow-up will be performed after 6 months of definitive prosthesis placement (ie, a cumulative period of 9 months following implant placement), and all parameters will be assessed as stated previously. At the end of the treatment, all patients will be asked to complete a quality of life (QoL) assessment questionnaire to determine the patient’s perspective before and after dental implant treatment.

CBCT recordings will be done using a small sized field of view of approximately 50 mm in diameter, which has an effective dose of approximately 54µSv [18].

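### The plan classes implants with ISQ 55 or below as unsuitable for immediate loading, then loads every implant within 7 days

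*Protocol article*

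**What the plan says.** In the protocol article, Operative Assessment has ISQ measured once the implant is in place and sets out how the reading is to be understood. A value of 70 or more is suitable for immediate loading, and 55 to 70 is moderate stability. The lowest class is "ISQ ≤55: low/questionable stability and not suitable for immediate loading".

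The next sentence gives the treatment instruction: "all implants will be loaded with a provisional prosthesis made of autopolymerizing resin". It fixes the time at no more than 7 days after surgery and attaches no ISQ condition.

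The Background gives the clinical rationale: "acceptable initial implant stability enables implant loading in as little time as 1 week".

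Follow-Up fixes the visits from surgery: "All patients will undergo 2 clinical follow ups, 3 months and 9 months after implant placement". At the first visit a provisional prosthesis is taken off, and then "The implant will then be loaded with a definitive prosthesis, and a CBCT will be recorded".

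The abstract's Results counts implants at placement: "A total of 30 dental implants will be placed in patients with a nonsyndromic orofacial cleft". The abstract's Objective is "determining the treatment outcome of immediately loaded dental implants in patients with a nonsyndromic orofacial cleft".

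**The concern.** The scale is worded as a judgement on whether an implant should be loaded early, and the Background makes early loading depend on adequate stability. A surgeon reading 55 or less is therefore told by one sentence that loading is unsuitable and by the next to load.

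What is at stake is first of all patient care. The sites are grafted clefts, and the abstract's Conclusions itself speaks of the "feasibility of immediately loaded dental implants in compromised bone sites such as those presented in cleft patients". Participants may be as young as 16 to 18, since entry is above 16 years and a parent or guardian may consent. Under the literal instruction, the patients with the weakest initial fixation receive the treatment that the plan's own criterion advises against. If a surgeon follows the scale instead, the plan offers that patient no prosthesis schedule.

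**Working it through.** **1. The statements side by side for an implant reading 55 or less**

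| Place in the protocol article | What it implies for this implant |
|---|---|
| Operative Assessment, ISQ scale | Not suitable for immediate loading |
| Operative Assessment, next sentence | Loaded within 7 days, like every other implant |
| Background | Early loading presupposes acceptable stability; no threshold or action given |
| Inclusion and Exclusion Criteria | Silent on ISQ, and could not screen for it, because ISQ is known only after placement |
| Follow-Up | Assumes a provisional prosthesis is in place to be removed at 3 months; no deferred path |
| Results (statistical methods) | No rule for low-ISQ implants |

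The first two rows cannot both be followed, and none of the others decides between them.

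**2. How often it might arise**

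The documents give no frequency of ISQ 55 or below, so the share q is assumed. Implants are treated as independent. With 30 implants (Sample Size Calculation), the expected number is 30 × q, and the chance of at least one is 1 − (1 − q)^30.

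| Assumed q | Expected number | Chance of at least one |
|---|---|---|
| 2% | 0.6 | 45% |
| 5% | 1.5 | 79% |
| 10% | 3 | 96% |
| 20% | 6 | 99.9% |

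The chance passes one half at q = 1 − 0.5^(1/30), about 2.3%. The table shows what each assumption implies. It does not show which assumption is right.

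**3. The plan's own precision figure**

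Inputs from Sample Size Calculation: success 95%, margin 8 points, 95% confidence, 28 implants, 5% loss, 30 in total.

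- n = 1.96² × 0.95 × 0.05 / 0.08² = 28.5, against 28 stated.
- 28 / 0.95 = 29.5, which rounds up to 30, as stated.
- Half-width with 28 evaluable = 1.96 × √(0.95 × 0.05 / 28) = 8.1 points.

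The plan's figures reproduce to within rounding.

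**4. Precision if low-ISQ implants are deferred**

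Start from the 28 evaluable after the planned loss and let an assumed share f be deferred. The number immediately loaded is 28 × (1 − f). The half-width is 1.96 × √(0.0475 / number). The number to place in order to keep 28 is 28 / 0.95 / (1 − f), rounded up.

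| Assumed f | Immediately loaded, evaluable | 95% half-width | Implants to place to keep 28 |
|---|---|---|---|
| 0 | 28 | 8.1 points | 30 |
| 10% | 25.2 | 8.5 points | 33 |
| 20% | 22.4 | 9.0 points | 37 |
| 30% | 19.6 | 9.6 points | 43 |

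**The case against.** The best reply is that the answer may lie in material not shown. Figure 1 summarises the methodology and has ISQ in its legend. The record sheet has a surgical section covering implant placement. The loading sentence opens by invoking an immediate loading protocol and cites a source for it. Any of these could carry a stability condition, and a journal article condenses the full protocol. This lowers certainty about what surgeons will actually do. It does not make the two adjacent sentences agree: this is a treatment rule stated in two incompatible ways, not a detail left out. If a branch exists elsewhere, the text still has to match it.

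Three stronger readings are tempting, and the documents do not support them.

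- A reader might infer that the success rate will be biased upward because low-stability implants drop out. Taken literally, the plan counts 30 implants at placement, loads all of them and dates both visits from placement, so nobody is dropped. A bias would need surgeons to depart from the instruction and the analysis then to omit those implants. Neither is stated.
- A reader might infer that the 55 to 70 class also lacks a loading decision. The scale gives none, but the next sentence loads every implant and nothing calls moderate stability unsuitable. The conflict is confined to 55 and below. The shared endpoint matters only at 55.
- A reader might infer that surgeons will handle such cases differently from one another. The trial has one centre, and the number of implant surgeons is not given.

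It is also fair to say that the choice between success among all placed and among immediately loaded implants is commonly left to a statistical analysis plan. Its absence here is not part of this point.

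**Conclusion.** The point stands for implants with ISQ 55 or below. The visible text declares them unsuitable for immediate loading and then orders it, and the follow-up schedule assumes it was done. This is a patient-care contradiction that should be fixed. It is not a demonstrated flaw in the success estimate.

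Its frequency is unknown. The conflict is more likely than not to arise at least once only if low readings exceed about 2.3% of implants, assuming independence. Confidence is medium, because the figure, the record sheet and the cited loading source could not be checked.

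**What to change.** - Make the loading sentence conditional, so that an implant reading 55 or less at placement is not immediately loaded. Alternatively, state and justify that such implants are loaded despite the scale.
- Assign the value 55 to one class only.
- State when a deferred implant receives its prosthesis, and keep its 3- and 9-month visits dated from placement.
- Keep all 30 placed implants in the report and state how many were deferred.

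The change to the text is a few sentences. The real cost is that fewer implants are immediately loaded, so success among them is estimated less precisely, by the half-widths shown in the working. Holding 28 evaluable would mean placing 3, 7 or 13 more implants at 10%, 20% or 30% deferred. That is out of proportion for a wording correction with an unknown deferral rate. It is better to keep 30 and restate the 8-point margin as what the number actually loaded will support.

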### Follow-Up

All patients will undergo 2 clinical follow ups, 3 months and 9 months after implant placement. At the first follow-up after a period of 3 months following immediate implant loading, the provisional prosthesis will be removed, and clinical and radiological parameters will be measured. Clinical parameters will include probing depth, bleeding on probing, suppuration, pain or tenderness in the implant area, and implant stability using ISQ values. The implant will then be loaded with a definitive prosthesis, and a CBCT will be recorded. A second follow-up will be performed after 6 months of definitive prosthesis placement (ie, a cumulative period of 9 months following implant placement), and all parameters will be assessed as stated previously. At the end of the treatment, all patients will be asked to complete a quality of life (QoL) assessment questionnaire to determine the patient’s perspective before and after dental implant treatment.

CBCT recordings will be done using a small sized field of view of approximately 50 mm in diameter, which has an effective dose of approximately 54µSv [18].

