**Methods:**

Patients meeting the set criteria will be sequentially enrolled until a sample size of 30 dental implants is met and will undergo the proposed treatment according to the predecided protocol. All patients will be followed up at the designated time intervals to record various clinical and radiographic parameters. Implant success will be defined based on the criteria elucidated by Misch et al in the Pisa, Italy Consensus. A quality-of-life assessment questionnaire will also be recorded at the end of patient’s follow-up to determine their acceptance of the treatment.

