### QoL Assessment Questionnaire

A QoL assessment questionnaire for the cleft population will be used to record their pre- and post-treatment experience with dental implant–based treatment.

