Success of dental implants is not only dependent on the achieved primary stability and subsequent osseointegration but also dictated by the soft tissue condition in the implant region. Cembranos et al [26], in their retrospective analysis of 47 implants, highlighted the importance of periodontal profile assessment along with measurements of bone levels to determine the success of implant-based treatment in cleft patients. Clinical and radiological evaluations of implant and adjacent sites in the form of probing depths, plaque and gingival indices, and marginal bone loss were also given importance in a similar analysis undertaken by Alberga et al [10].

Considering the global prevalence of deformity and lack of research in the field of immediately loaded dental implants in cleft patients, this study is formulated with an aim of evaluating the clinical and radiographic success of dental implant at the cleft site in orofacial cleft patients. At the same time, the proposed work also emphasizes the importance of having a preformed patient record sheet and need for recording various clinical and radiographic parameters and thus, has formulated a dentist-friendly and comprehensive record sheet that will be utilized in the study.

Apart from providing patients with enhanced functionality, replacement of the missing tooth will also enhance a patient’s aesthetics and their subsequent self-perception. During any rehabilitative procedure, it is important to know how the patient feels about it and what changes they see in their life pre- and post-treatment. This can be successfully evaluated using a QoL questionnaire. According to Burckhardt and Anderson [27], a QoL questionnaire encompasses details concerning material and physical well-being; relationships with other people; social, community, and civic activities; personal development and fulfilment; and recreation. QoL provides a meaningful way of determining the patient’s psychological improvement and making pre- and post-treatment comparisons.

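### The visible text schedules the quality-of-life questionnaire only at the end, so the 'before' rating in the planned pre/post comparison is recalled, not measured

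*Protocol article*

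**What the plan says.** Two places in the protocol article fix when QoL is collected.

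- **Follow-Up**, after the 9-month visit: "At the end of the treatment, all patients will be asked to complete a quality of life (QoL) assessment questionnaire", with the purpose "to determine the patient’s perspective before and after dental implant treatment".
- **Abstract, Methods**: "A quality-of-life assessment questionnaire will also be recorded at the end of patient’s follow-up to determine their acceptance of the treatment".

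Two further places say what the questionnaire is for, without giving a time.

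- **QoL Assessment Questionnaire**: the instrument "will be used to record their pre- and post-treatment experience with dental implant–based treatment".
- **Discussion**: "QoL provides a meaningful way of determining the patient’s psychological improvement and making pre- and post-treatment comparisons".

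The **Operative Assessment** section lists what is recorded before tertiary grafting and before implant surgery. It names the oral hygiene index at both points and compares the two readings. It does not name QoL.

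**The concern.** A pre/post comparison needs a value from before treatment. As written, one administration at the end supplies both halves, so the first half is a recollection. It comes from patients who know that they have been treated and how the treatment went. The trial has one arm, so no comparator group shares the same recall error and could cancel it.

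At stake is whether a reported QoL change can be read as a change at all. If the recalled rating is systematically too low or too high, the difference reflects that error together with any real effect, and no later analysis can recover a baseline that was not collected. This is more than detail left out of a condensed article: the timing is stated twice and consistently, and the same article does describe a baseline reading where it plans one (oral hygiene).

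**Working it through.** **Is there a figure to reproduce?** The article states none for QoL. Its sample size rests on the implant success proportion alone and has no bearing here. The point is settled by setting the statements side by side and adding up the schedule.

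**Step 1. Timing against purpose.**

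| Section | Time of QoL | Use of QoL |
|---|---|---|
| Abstract, Methods | End of follow-up | Acceptance of treatment |
| Follow-Up | End of treatment | View before and after treatment |
| QoL Assessment Questionnaire | Not given | Pre- and post-treatment experience |
| Discussion | Not given | Pre/post comparison |
| Operative Assessment | QoL not named | Oral hygiene index taken before grafting and before implant surgery |

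Every statement that gives a time gives the end. Three of the four statements on use need a pre-treatment value.

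**Step 2. Length of recall.** Inputs: the last follow-up is 9 months after implant placement (Follow-Up); the planning CBCT is 3 to 6 months after grafting (Operative Assessment).

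- 'Before' means before implant placement: at least 9 months.
- 'Before' means before tertiary grafting: 3 + 9 = 12 months to 6 + 9 = 15 months. This assumes placement at about the time of the CBCT. The article gives no interval from CBCT to placement, so any delay adds to these figures.

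**Step 3. What recall error could do (illustration only).** The inputs here are assumptions, not figures from the article: up to 30 patients with one implant each, standard deviation 1 at both times, pre/post correlation 0.5, no true change, and a two-sided 5% paired test by normal approximation.

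- SD of the difference = √(2 × (1 − 0.5)) = 1.
- With a systematic recall shift of b SD and n patients, λ = b√n.
- Probability of a significant result = Φ(λ − 1.96) + Φ(−λ − 1.96).
- Example, b = 0.3 and n = 30: λ = 0.3 × 5.477 = 1.643, so Φ(−0.317) + Φ(−3.603) ≈ 0.376.

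| Recall shift (SD) | n = 20 | n = 30 |
|---|---|---|
| 0 | 5% | 5% |
| 0.2 | 15% | 20% |
| 0.3 | 27% | 38% |
| 0.5 | 61% | 78% |

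The test is two-sided, so a shift in either direction gives the same rates. The table shows only that a modest shift would matter at this sample size. It does not show that such a shift will occur.

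**Step 4. Missing values.** The sample size section allows 5% loss: 0.05 × 30 = 1.5, covered by 2 extra implants. With collection at the end, a patient who is lost contributes nothing on QoL, so even a check of whether completers differed at baseline is impossible.

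**The case against.** The strongest case on the other side has five parts.

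- **QoL is peripheral.** It is absent from the Aim, the Objectives and the sample size, and the Results section names no QoL test. This stands, and it limits the weight of the point.
- **The article never says 'only'.** The QoL Assessment Questionnaire section would fit two administrations. Figure 1, whose legend lists QoL, is not shown, and neither is the questionnaire. This also stands: a baseline could be scheduled there. If so, the Abstract and Follow-Up text would still need correcting. A reader might infer that certainly no patient will have a baseline; the documents support only that the visible text schedules none.
- **Part of the purpose needs no baseline.** The Abstract speaks of acceptance of treatment, and the Discussion sentence is a general remark about QoL instruments. That is fair, but Follow-Up and the questionnaire section both commit to a 'before' view. The pre-treatment record of how the patient perceives the existing prosthesis (Prosthetic Considerations) is not a QoL score.
- **A measured comparison has its own weakness.** A patient's internal standard may move between two dates (response shift). Rating both periods on one day uses a single standard, at the price of recall error. This stands: the fix exchanges one problem for a smaller set of problems and does not supply a control group.
- **Bias in favour of treatment is not shown.** A reader might infer that an improvement is likely even with no real change. The document gives no basis for the size or the direction of the error, so that reading goes too far.

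A reader might also infer that patients whose implant failed drop out of the QoL data. Follow-Up says that all patients will be asked, and nothing visible excludes those with a failed implant. Only patients lost to follow-up are certain to be missing, and they would lack a paired change under any schedule.

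**Conclusion.** The point holds for the QoL comparison and no further. On the visible text, the pre-treatment rating is recalled after at least 9 months, or about 12 to 15 months or more counted from grafting if implants are placed at about the time of the planning CBCT. With no comparator, an apparent change cannot be separated from recall error. The size and direction of that error cannot be derived from the documents, and the rates in the illustration depend wholly on the assumed shifts and correlation.

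It would be wrong to extend this to the trial's main results: implant success, survival, stability and bone-level findings do not use the questionnaire. The item should be fixed because the remedy is cheap and the loss is irreversible for each patient treated without a baseline. It does not undermine the trial. The conclusion assumes that the figure not shown contains no earlier administration.

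**What to change.** - Give the same questionnaire before treatment, at the existing pre-grafting assessment or at the latest before implant placement. State which of the two defines 'before'.
- Give it again at 9 months to all patients, saying explicitly that those with a failed implant are included.
- Correct the timing in the Abstract and in Follow-Up to match, and check that Figure 1 agrees.
- Analyse the paired change with a 95% confidence interval, and compare the baseline values of patients with and without a 9-month rating.
- For patients already treated without a baseline, label the 'before' rating as retrospective and report it separately from measured changes.

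**Cost.** One extra questionnaire at a visit already planned, and a minor amendment. The measured change would still be uncontrolled and open to response shift, and the report should say so.
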